### Study design

The two studies in Burkina Faso and Nepal are designed as cluster randomised trials with an equal number of schools randomly allocated to two core study arms (A, B) and with a cohort of children followed in two consecutive surveys, at baseline and 1-year follow-up. Two additional study arms are included in Nepal (C, D). The four study arms are designed as follows:arm A: school garden programme and complementary nutrition and WASH interventions;arm B: no interventions, i.e. controls;arm C: school garden programme without nutrition and WASH interventions; andarm D: nutrition and WASH interventions without the school garden programme.

Each arm comprises four schools. Figure 1 shows the study design with the different study arms for Burkina Faso and Nepal. In both countries, schools of arm A will receive the complementary school garden, nutrition and WASH intervention package starting in March 2015. In Nepal, the interventions from arms C and D will be implemented over the same period. In both countries, the control schools of arm B will benefit from the school garden intervention in the year following the interventions.

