### Sample size

Two separate sample size calculations were conducted for the two study designs of Burkina Faso and Nepal. For the sample size calculation of the study in Burkina Faso, the prevalence of intestinal parasitic infection in children aged 8–14 years was selected as the primary outcome in the comparison between high- and low-risk of intestinal parasitic infection in children. The power calculation was based on the assumption of:an average intestinal protozoa and helminth infection rate across schools of 40 % [33];a coefficient of variation of 10 % across schools; anda proportion of high risk children of 25 %.

A Monte Carlo simulation with 5000 iterations shows that a total of 400 children from eight schools (i.e. 50 children per school) would provide 85 % power for detecting a significant difference in infection rates between high- and low-risk children at the usual level of 5 % under these assumptions and for a true odds ratio of 2. Recruitment will be increased by 10 % to account for drop-outs or non-participation, which leads to an optimal sample size of at least 440 children.

The sample size calculation for the study in Nepal was also based on the prevalence of intestinal parasitic infections in children aged 8–14 years as the primary outcome. The power calculation was based on the assumption of:the prevalence rate of intestinal protozoa and helminth infection is 30 % [34] and this rate will remain in steady state in the absence of any intervention;probability of new intestinal protozoa and helminth infection at the 1-year follow-up will be reduced by at least 10 % through the implementation of the complementary nutrition and WASH intervention package; anda coefficient of variation of 10 % across schools.

A Monte Carlo simulation with 5000 iterations shows that a total of 640 schoolchildren from 16 schools (i.e. 40 children per school) would provide 80 % of power for detecting a significant difference in infection rates between the four study arms. Recruitment will be increased by 10 % accounting for drop-outs and non-participants, which leads to an optimal sample size of at least 704 children.

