The two studies in Burkina Faso and Nepal within the frame of the overall VgtS project that we describe here will support the reinforcement of this recent attention on schoolchildren’s nutrition and health by focusing on schools as an entry point for health promotion, infection control and life-skills education. Moreover, the studies will contribute to fill existing data gaps on schoolchildren in these two countries, concurrently identifying their nutritional and health challenges and needs. The data collected will serve to inform the design of appropriate and tailored school-based interventions with close participation of the local community, school teachers and directors, as well as with the local research and VgtS project team. The precise set of interventions will be developed after the baseline survey in Burkina Faso and Nepal. The interventions will be designed with a multidisciplinary team of educators, epidemiologist, nutritionist, parasitologists and WASH experts in order to improve water quality, sanitary and hygiene environments and to translate the nutritional and health risk factors into effective educational messages, thereby encouraging schoolchildren to change their behaviour.

The two studies also aim to address the scientific research gap by conducting rigorous intervention studies and quantifying the possible effects of complementary school garden, nutrition and WASH interventions. With the two particular study designs as suggested in Burkina Faso and Nepal, we will be able to analyse the different types of school garden, nutrition and WASH intervention packages. While in Burkina Faso the focus will be on the comparison of integrated and complementary school garden, nutrition and WASH interventions (arm A) as compared to the control schools with no interventions (arm B); in Nepal, we will additionally be able to conduct comparisons between these two study arms to the school garden intervention schools (arm C) and the nutrition and WASH intervention schools (arm D).

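### The 80% power stated for the four-arm Nepal comparison does not follow from the inputs given; a 10-point fall in prevalence yields about 49–69%, a relative 10% fall about 8–13%

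*Protocol article*

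**What the plan says.** The Sample size section of the protocol article names the prevalence of intestinal parasitic infection as the primary outcome for Nepal. It assumes that "the prevalence rate of intestinal protozoa and helminth infection is 30 % [34] and this rate will remain in steady state" without intervention, that the "probability of new intestinal protozoa and helminth infection at the 1-year follow-up will be reduced by at least" 10%, and a "coefficient of variation of 10 % across schools". The reduction is said to come "through the implementation of the complementary nutrition and WASH intervention package". From a 5000-iteration simulation it reports that 640 children, 40 in each of 16 schools, give 80% "power for detecting a significant difference in infection rates between the four study arms".

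Under Study design, "Each arm comprises four schools". Nutrition and WASH are given in arms A and D. Arm C has the garden alone, arm B is the control, and A and B are called the core arms. The Discussion adds that "in Nepal, we will additionally be able to conduct comparisons between these two study arms to the school garden intervention schools (arm C"), and likewise to arm D. Nowhere are arms pooled, no effect is assumed for the garden, and the 10% is not identified as absolute or relative.

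**The concern.** The section prints a power figure, its inputs and the comparison it refers to, so the three can be checked against each other. They do not agree. Two ambiguities make this worse. The 10% may mean 30% to 20% or 30% to 27%. The outcome is named as prevalence, yet the effect is placed on the probability of new infection, and no risk of new infection is given.

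Readers will use the 80% to judge what a non-significant Nepal result means. If the real power for the stated four-arm comparison is nearer one half to two thirds, or about one tenth, a null result carries far less information than the article suggests. The same applies to A versus B. The article states no power for that comparison, but it is the core contrast.

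**Working it through.** **Inputs.** From Sample size: control prevalence 0.30; 40 children per school; coefficient of variation 0.10; effect of 10% through nutrition/WASH. From Study design: four schools per arm, with nutrition/WASH in A and D. Dropout is added afterwards (640 to 704) and does not affect power at 640. Two-sided 5% is an assumption, since the article states 5% only for Burkina Faso.

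**Variance of one school's observed proportion:** p(1−p)/40 + (0.10p)².
- p = 0.30: 0.21/40 + 0.0009 = 0.00615
- p = 0.20: 0.16/40 + 0.0004 = 0.00440
- p = 0.27: 0.1971/40 + 0.000729 = 0.00566

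**Attempt to reproduce the 80%: four-arm test, 3 df, 20,000 simulated trials.** Ranges run from a school-level F test, through a chi-square with design-adjusted variance, to a chi-square that ignores clustering.

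| Arms lowered | School-level F | Adjusted chi-square | Clustering ignored |
|---|---|---|---|
| A and D at 20% | 48–49% | 63% | 69% |
| A only at 20% | 35% | 47% | 56% |
| A, C and D at 20% | 40% | 52% | 58% |
| A and D at 27% | 8% | 9% | 13% |

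None reaches 80%, even with clustering ignored, which favours the plan.

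**A versus B (4 v 4 schools).** Power = Φ(difference/SE − 1.96).
- 30% v 20%: SE = √[(0.00615 + 0.00440)/4] = 0.0514; 0.10/0.0514 = 1.95; power 50%. By t test on school proportions (6 df) it is 37–38%. With clustering ignored it is 54%, and one-sided (normal) 62%.
- 30% v 27%: SE = √[(0.00615 + 0.00566)/4] = 0.0543; 0.03/0.0543 = 0.55; power 8%. Other variants give up to 9%.
- By the normal formula, 80% needs a fall to about 16%.

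**Pooled A+D versus B+C (8 v 8 schools).**
- 30% v 20%: SE = √[(0.00615 + 0.00440)/8] = 0.0363; 0.10/0.0363 = 2.75; power 79%. By t test (14 df) it is 73%.
- 30% v 27%: SE = 0.0384; 0.03/0.0384 = 0.78; power 12%. By t test it is about 11%.

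**Reading the effect as new infection.** Take the 70% uninfected at baseline: 0.70 × 40 = 28 per school. Under steady state, 0.30 = 0.30s + 0.70r, where s is the share of infected children still infected a year later and r is the annual risk. So r cannot exceed 0.30/0.70 = 0.43, and any value below that is possible.
- Four-arm test, A and D lowered by 10 points, adjusted chi-square: r = 0.13 gives 94%, 0.15 gives 86%, 0.16 gives 82%, 0.17 gives 79%, 0.20 gives 68%. The 80% line is crossed at about r = 0.165. By school-level F it is crossed at about 0.13 (81%).
- Ten points off 0.165 removes 0.10/0.165 = 61% of new infections. Off 0.13 it removes 77%.
- With a relative 10% cut, the four-arm test stays at or below about 26% at every risk tried.
- If the outcome is prevalence but only new infections fall by 10 points, prevalence drops by 0.70 × 10 = 7 points, to 23%. Power is then 26% for A versus B and 47% pooled, so the 30%-to-20% reading above is the generous one.

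**The case against.** The strongest reply is that the figure comes from a simulation the article only summarises, and that the effect is worded as a cut in new infections within a followed cohort. On that wording a four-arm test can reach 80% without pooling if the annual risk is about 0.165 or lower. Steady state would then imply that about 62% of infected children remain infected (1 − 0.70 × 0.165/0.30), which cannot be excluded from the article. Other unstated settings also get there: an additional 10-point garden effect (88–97% for the four-arm test), or adjustment for baseline with a within-child correlation near 0.7 (about 83% for A versus B).

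This stands as a limit on the conclusion. A reader might infer from the 79% that the authors must have simulated A+D versus B+C, or that 80% holds only there. The article supports neither inference: it never mentions that contrast, and a different model could have produced the number. Nor should the point be read as showing that no simulation could give 80%.

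The reply does not rescue the paragraph as printed. It names prevalence as the outcome, states no risk of new infection, no garden effect and no baseline correlation, and credits the effect to nutrition and WASH. Leaving simulation detail to a fuller document is normal. Printing inputs that do not yield the printed result is a different matter.

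It is also true that the article claims no power for pairwise tests; the Discussion says only that they can be made.

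**Conclusion.** The point holds. On the inputs the Sample size section states, with prevalence as outcome and two-sided 5% assumed, the 80% for a four-arm comparison is not delivered. A 10-point fall in A and D gives about 49–69%, and a relative 10% fall about 8–13%. The core A versus B comparison has about 38–50% and 8–9% respectively.

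Two routes come near 80%, and both need something the article does not say. One is the pooled nutrition/WASH contrast with a 10-point fall (73–79%). The other is a four-arm test of new infections at an annual risk at or below about 0.165 (0.13 by school-level F) falling by 10 points, which removes 60% or more of new infections.

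A reader might go further and conclude that A+D versus B+C ought to become the primary contrast. The article does not support that. It calls A and B the core arms, and pooling assumes that the garden does not modify the nutrition/WASH effect, so the change would be a debatable redesign. What must be corrected is the power statement.

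**What to change.** In the Nepal part of Sample size, state:
- whether the 10% is absolute (30% to 20%) or relative (30% to 27%);
- whether the powered outcome is prevalence or new infection and, if new infection, the assumed annual risk without intervention;
- which contrast and test were simulated, and at what significance level.

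Then restate the power for that contrast, and give the power for A versus B beside it: on prevalence, about 38–50% at 30% to 20%, or about 8–9% at 30% to 27%. If the simulated contrast was nutrition/WASH versus no nutrition/WASH (A+D versus B+C) with a 10-point fall, say so and quote about 73–79%, noting that it assumes the garden does not alter the effect.

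The cost is one re-run of the simulation, a reworded paragraph and a less favourable stated power. Schools, children and arms stay as they are.

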### Data management and analysis

Quantitative data from stool and urine examinations, anthropometrics and Hb measurements will be entered in Microsoft Excel 2010 (Microsoft; Redmond, USA). A double data entry system will be used to ensure data quality. Data will be evaluated for discrepancies and validated after removing inconsistencies. The z-score values for height-, weight- and BMI-for-age relative to the WHO 2007 reference will be calculated using WHO AnthroPlus (WHO; Geneva, Switzerland). Statistical analyses will be carried out with Stata version 13 (StataCorp; College Station, USA). Analysis of baseline data will be conducted to describe the prevalence of malnutrition, intestinal parasitic infections, WASH conditions, KAP and basic socioeconomic characteristics. Logistic regression models will be employed to estimate associations of malnutrition, intestinal parasitic infections and anaemia with risk factors.

FGDs and in-depth interviews (IDIs) will be transcribed, translated into English by bilingual research assistants and entered as Microsoft Word documents into MAXQDA version 11 (VERBI GmbH 2012; Berlin, Germany) for data coding and analysis. Main themes will be identified and coded in order to categorise explanations and descriptions of nutritional and health related perceptions and issues.

Longitudinal analysis will be conducted to evaluate the intervention effects of the complementary interventions under study. The results from the different study arms will be compared at the end of the 1-year intervention period.

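### Nepal: the assumed effect, the comparison said to have 80% power and the core comparison are three different contrasts, and power and significance depend on which one decides

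*Protocol article*

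**What the plan says.** Nepal has four arms of four schools each: A (garden plus nutrition and WASH), B (control), C (garden only) and D (nutrition and WASH only). Four places in the protocol article bear on which comparison decides the primary outcome.

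- **Methods/Design, Study design.** The trials have "an equal number of schools randomly allocated to two core study arms (A, B"), and C and D are described as additional arms for Nepal. This points to A v B.
- **Methods/Design, Sample size, effect assumed.** The probability of new infection at one year "will be reduced by at least 10 % through the implementation of the complementary nutrition and WASH intervention package". No effect is assumed for the garden.
- **Methods/Design, Sample size, power claimed.** The 640 children in 16 schools are said to give 80% power "for detecting a significant difference in infection rates between the four study arms".
- **Discussion.** After A v B, "in Nepal, we will additionally be able to conduct comparisons between these two study arms to the school garden intervention schools (arm C") and also to arm D. With A v B, that makes five pairs: AB, AC, AD, BC and BD.

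The section Data management and analysis does not choose among these: "The results from the different study arms will be compared at the end of the 1-year intervention period". The only significance level given is in the Burkina Faso calculation, "at the usual level of 5 % under these assumptions".

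**The concern.** A sample-size statement should say which contrast the sample size serves. Here the effect assumption and the power claim, in the same section, refer to different contrasts, and the design section gives prominence to a third.

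These are different questions. A v B asks whether the full package beats nothing. A+D v B+C asks whether nutrition and WASH help, averaged over garden and no garden. A four-arm test asks whether any arm differs from any other. They use different numbers of schools (8, 16 and 16), so their power differs widely. If the choice stays open until follow-up data are in, the finding can rest on whichever contrast is significant. A reader also cannot tell which question the 80% power refers to.

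**Working it through.** **Inputs from the Sample size and Study design sections.** Prevalence 30% without intervention; a 10% reduction; coefficient of variation (CV) 10% across schools; 40 children per school; 4 schools, so 160 children, per arm.

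**Assumptions.** Two-sided 5% for Nepal, where no level is stated. The 10% is taken first as points (30% to 20%), then as relative (30% to 27%), and is applied to prevalence because no probability of new infection is given. The effect is placed in arms A and D.

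**Clustering.** ICC = CV² × p/(1−p) = 0.01 × 0.3/0.7 = 0.0043. Design effect = 1 + 39 × 0.0043 = 1.167. Effective size = 160/1.167 = 137.1 per arm, or 274.2 per pair of arms.

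**Trying to reproduce the 80% (30% v 20%).** For two groups of effective size n with mean prevalence 0.25, power = Φ[(0.10 − 1.96·√(2×0.25×0.75/n)) / √((0.3×0.7 + 0.2×0.8)/n)].

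- A v B, n = 137.1: Φ[(0.10 − 0.1025)/0.0520] = Φ(−0.05) = 48%.
- A+D v B+C, n = 274.2: Φ[(0.10 − 0.0725)/0.0367] = Φ(0.75) = 77%.
- Four-arm test, 3 df: noncentrality = 137.1 × 4 × 0.05²/(0.25×0.75) = 7.31, against a critical value of 7.81; power 61%.

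Ignoring clustering gives 54%, 83% and 69%. The stated 80% is therefore not reproduced for the four-arm comparison that it names. The margin A+D v B+C comes nearest.

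**Simulation at school level** (4 schools of 40 per arm, school SD 10% of prevalence, pooled variance on 12 df), beside the formula:

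| Contrast | 30% v 20%: formula | simulated | 30% v 27%: formula | simulated |
|---|---|---|---|---|
| A v B | 48% | 44% | 8% | 8% |
| Four-arm test | 61% | 48% | 9% | 8% |
| A+D v B+C | 77% | 72% | 12% | 11% |

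Without clustering the highest value for 30% v 27% is 13%.

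**New infections instead of prevalence.** Among the 70% uninfected at baseline there are 112 children per arm. For assumed one-year risks of 15%, 20%, 30% and 40%, each falling by 10 points, A+D v B+C has power 93%, 82%, 64% and 53%. A value near 80% is thus attainable (risk 20% to 10%), but that risk is not in the article.

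**How often the choice changes significance** (same simulation):

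| Pair of tests | 30% v 20% | 30% v 27% |
|---|---|---|
| A v B and A+D v B+C disagree | 32% | 10% |
| Four-arm test and A v B disagree | 23% | 8% |
| Four-arm test and A+D v B+C disagree | 25% | 9% |

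If only the garden worked (A and C 20%, B and D 30%), A v B would be significant in about 43–44% of trials and A+D v B+C in 5%. The second test does not address the garden, so this is correct behaviour; it shows that the two answer different questions.

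**One illustrative data set.** Infected children A 32, B 50, C 46, D 42 of 160 each, with variance multiplied by 1.167:

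- A v B: 20.0% v 31.25%, z = 0.1125/0.0527 = 2.13, p = 0.033.
- A+D v B+C: 74/320 v 96/320, z = 0.06875/0.0377 = 1.82, p = 0.068.
- Four-arm test: chi-square 4.91 on 3 df, p = 0.18.

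**Error rate for the five named pairs, no effect anywhere.** If each is tested at an unadjusted two-sided 5% and any one counts as a claim: 17% (pooled school-level t, 12 df), 18% (normal) or 18.5% (separate t-tests, 6 df). If a four-arm test must be significant first, or if A v B alone decides, it is about 5%.

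**The case against.** Much can be said for the plan. This is a condensed article, and the order of tests and control of multiplicity are commonly left to an analysis plan that is not shown. The words core and additional are an informal ranking, and the stated goal concerns the combined package, so A v B is a natural primary. The contrast A+D v B+C is nowhere named; it is inferred from the effect assumption, and the wording for the package could be taken to mean arm A alone. Tests with different power will often differ in significance.

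All of this stands, but it does not remove the mismatch. An unseen analysis plan can add detail; it cannot make the published effect assumption, power claim and core designation agree. The informal ranking favours A v B, yet the power statement does not follow it, and on the article's figures A v B has the lowest power of the three.

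Three stronger readings are tempting and not supported.

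- A reader might infer a 17–18% chance of a false claim. That needs five unadjusted tests with any one decisive, a rule the article does not state; four of the five pairs appear only in the Discussion, as comparisons the design makes possible.
- A reader might infer that the choice of test can reverse the conclusion. The checks show significant turning to non-significant, not a change in the direction of effect.
- A reader might infer that the 80% is an error. The simulated test, the probability of new infection and the meaning of the 10% are not given, so failure to reproduce it proves nothing.

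**Conclusion.** The concern holds as an inconsistency in the published text: for one primary outcome in Nepal, the assumed effect, the powered comparison and the core comparison are three different contrasts. With the 10% read as points, power ranges from about 44–48% (A v B) through 48–61% (four-arm test) to 72–77% (A+D v B+C), and the first and last disagree on significance in about 32% of trials. Read as relative, all three have only about 8–13% power and the disagreement falls to about 10%.

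These figures rest on a two-sided 5% level, on applying the reduction to prevalence, and on an effect in A and D only. The absence of alpha control is not in itself the finding. The point should be corrected before the follow-up data are analysed, but it does not invalidate the design.

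**What to change.** In Sample size and in Data management and analysis, name one primary contrast for Nepal. Replace the reference to the four arms in the power statement with that contrast and restate its power, giving the significance level, whether the 10% is relative or in points, and the assumed probability of new infection.

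Suggested text: *The primary comparison in Nepal is the effect of nutrition and WASH (arms A+D v B+C) on intestinal parasitic infection at the 1-year follow-up, at a two-sided 5% level, from one model with terms for garden and for nutrition/WASH and with school as the cluster. If it is significant, A v B and then the garden effect (A+C v B+D) are tested in that order, each at 5%. The interaction and all other contrasts between arms are exploratory and reported with 95% intervals.*

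This primary matches the assumed effect and uses all 16 schools. If the sponsor prefers to keep the core contrast, putting A v B first in the same fixed order is acceptable, with its lower power stated.

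The cost is wording only, with no further schools, children or data. In return, contrasts below the first failed step carry no confirmatory claim, and the A+D v B+C effect is an average over garden and no garden, to be read with the interaction estimate.
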